### Population and sample

Adults aged ≥18 years be selected through convenience sampling from the community based on the following criteria: a) newly diagnosed hypertension (defined as blood pressure ≥140/90 mmHg); b) uncontrolled hypertension (defined as blood pressure ≥140 mmHg in individuals with a previous diagnosis of hypertension or who are currently on antihypertensive treatment); and/or c) known hypertensive individuals not regularly attending cardiovascular risk management programs at primary care centers. Exclusion criteria include established cardiovascular disease (e.g., coronary artery disease, myocardial infarction, heart failure, arrhythmias, cardiomyopathies, peripheral arterial disease, stroke or transient ischemic attack, diabetes mellitus with macrovascular complications, or history of invasive cardiovascular procedures), chronic kidney disease requiring dialysis, intolerance to antihypertensive medications, and resistant or secondary hypertension. The exclusion of these people was based on the fact that these pathologies require individualized and specialized management at high levels of care, which exceeds the capabilities of a community-based strategy.

#### Intervention

The intervention will include the following components:

Identification of individuals with new or uncontrolled hypertension: RE-HOPE will strengthen the primary network through cardiovascular risk programs, which will promote its integration and institutionalization, a key step for the success of its implementation. In this framework, trained CHWs, supported by community leaders, will conduct active case finding in the community using a standardized screening protocol (Figure 1). Community leaders will facilitate engagement between CHWs and potential participants, organizing meetings, follow-up routes, and actions to increase access and coverage of healthcare services. Screening will occur door-to-door, during community outreach events, and at primary care facilities. After consent, individuals will undergo initial blood pressure measurement. If elevated blood pressure or another inclusion criterion is detected, a follow-up measurement will be scheduled within a week. Individuals with normal blood pressure will receive health education on healthy lifestyles and age-appropriate blood pressure monitoring recommendations (2) Those meeting hypertension criteria will be invited to participate, and informed consent will be obtained. Baseline sociodemographic and clinical data will also be collected.

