**Figure 1 F1:**
[figure not shown]
RE-HOPE study flowchart. Trained CHWs, supported by recognized community leaders, will conduct a door-to-door active community-based case finding using a standardized screening protocol. If hypertension is detected, a follow-up measurement will be scheduled within a week. Participants with hypertension will be referred to their assigned primary care provider based on their health insurance affiliation, using a standardized referral form. Once enrolled in a cardiovascular risk management program, home visits will be scheduled as part of the community-based intervention. BP, blood pressure; CHW, community health workers; CV, cardiovascular.

Referral to primary care providers: Participants with hypertension will be referred to their assigned primary care provider based on their health insurance affiliation, using a standardized referral form. A centralized team will submit participant lists via an online platform (e.g., OneDrive) to schedule medical appointments and ensure program enrollment. Participants and/or their families will be contacted by phone with appointment details. If a participant does not attend, they will be followed up to identify barriers and facilitate access to care. If a participant does not agree to assist, they will be excluded. Once enrolled in a cardiovascular risk management program, home visits will be scheduled as part of the community-based intervention (Figure 2).

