**Figure 3 F3:**
[figure not shown]
Follow-up visit schedule. The intervention includes five scheduled follow-up visits over 12 months. At each visit, participants will receive health counseling, blood pressure measurement, weight monitoring, and a review of their pharmacological treatment. BP, blood pressure.

Healthcare provider training: The research team will train CHWs in standardized blood pressure measurement techniques, strategies to enhance medication adherence, the use of data collection tools, health counseling, and assertive community engagement. Ongoing training sessions will also be held for healthcare professionals and technicians at primary care centers receiving study participants. Topics will include hypertension detection and management based on World Health Organization (WHO)-recommended fixed-dose combination therapy algorithms (15). The training is provided by health professionals who serve as operational coordinator and others health professionals.

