### Follow-up

CHWs will arrange appointments for home follow-up visits (months 1, 3, 6, 9, and 12), and blood pressure will be measured according to the standardized protocol. Additional data will be collected on anthropometric variables, physical activity habits, tobacco and alcohol use. The follow-up framework aligns with the guidelines of the International Society of Hypertension for hypertension management and the WHO guidelines (2, 15). Barriers to accessing antihypertensive medications and statins within the healthcare system will also be evaluated. If participants are found to have uncontrolled hypertension, they will be referred to their corresponding primary care center for medical evaluation and adjustment of antihypertensive therapy. In cases of critically elevated blood pressure (>180/100 mmHg), with or without signs of target organ damage, emergency care will be recommended.

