### Blood pressure measurement

Blood pressure will be assessed using a strictly standardized protocol. Participants will be instructed to avoid caffeine, smoking, and physical activity for at least 30 min before the assessment. The appropriate cuff size will be selected according to mid-arm circumference, and blood pressure readings will be recorded using a calibrated device in accordance with the manufacturer's specifications. Blood pressure will be measured with the participant seated comfortably after a rest period of at least 5 min in a quiet environment. During the measurement period, participants will remain seated with their back supported, feet flat on the floor, and legs uncrossed. The arm used for measurement will be uncovered and supported at heart level. Three consecutive measurements will be obtained at 1- to 2-minute intervals using validated automated upper-arm devices. For analysis, the average of the last two readings will be used to improve accuracy and reduce short-term variability. To minimize misclassification related to the white-coat effect, out-of-office blood pressure monitoring will be recommended when clinically indicated. All procedures will be conducted in accordance with the recommendations of the International Society of Hypertension (ISH) guidelines, ensuring methodological rigor and reproducibility (2).

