Despite its strengths and potential contributions to hypertension monitoring and control, this study will have some limitations. The single-arm design may limit our ability to attribute observed changes exclusively to the intervention because no comparator group will be included. In addition, methodological aspects such as convenience sampling may introduce selection bias and reduce the representativeness of the sample relative to the broader population of individuals with hypertension in Santander. It is important to note, however, that the strategy is specifically intended to identify and recruit individuals who do not usually access healthcare services through screening in primary care facilities. Furthermore, the exclusion of individuals with established cardiovascular disease and resistant hypertension may limit the generalizability of the findings to populations with more severe cardiovascular conditions. Nevertheless, the intervention was specifically designed for large-scale implementation in community settings within the primary care system rather than at higher levels of care. Accordingly, the findings should be interpreted with caution when extrapolating them to the overall population of individuals with hypertension.

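### Entry blood pressure may be read outside the home while all follow-up readings are at home, and neither the baseline reading nor its place is defined, so a setting difference may be counted as intervention effect

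*Protocol article*

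**What the plan says.** All places are in the protocol article.

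- **Entry readings.** Under Intervention: "Screening will occur door-to-door, during community outreach events, and at primary care facilities". The first reading is part of that screening. If it is raised, or another inclusion criterion is met, "a follow-up measurement will be scheduled within a week"; no place is given for this repeat. The text does not say whether the first reading, the repeat or a later one is the baseline value.
- **Other statements on place.** The Figure 1 caption is narrower: CHWs "will conduct a door-to-door active community-based case finding using a standardized screening protocol". The limitations paragraph of the Discussion mentions facilities again, in describing a strategy meant to "identify and recruit individuals who do not usually access healthcare services through screening in primary care facilities".
- **Follow-up readings.** Under Follow-up: "CHWs will arrange appointments for home follow-up visits (months 1, 3, 6, 9, and 12), and blood pressure will be measured".
- **Outcome and design.** The primary outcome is the change in systolic pressure from baseline to 12 months (Outcomes and measurements), compared within participants in a single arm (Study design).
- **Control of setting.** The Blood pressure measurement section standardises posture, cuff, rest, device and number of readings, but not place. On the white-coat effect it says: "To minimize misclassification related to the white-coat effect, out-of-office blood pressure monitoring will be recommended when clinically indicated". Data collection lists no item for place of measurement. The fixed effects under Clinical effectiveness outcomes are sex, region, age and anthropometric measures.

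**The concern.** In a single-arm before-after comparison, any systematic difference in measurement conditions between baseline and month 12 goes straight into the estimate, because there is no comparator in which it would cancel. Here the permitted conditions differ: baseline may be read at an event, in a clinic or at home, and month 12 is read at home. If pressure tends to differ between those settings, part of the reported change would be a change of place.

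The listed covariates cannot remove this. A main effect of sex, age or region that is constant over time does not absorb a shift that affects only the baseline reading. If place is not recorded at the time, no later analysis can recover it.

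This is separate from regression to the mean. It would arise even in participants who were not selected on a high reading.

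**Working it through.** **Step 1. Does the text allow the mismatch?**

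| Element | Place stated | Where |
|---|---|---|
| First reading | Home, outreach event or primary care facility | Intervention |
| Same, in the flowchart caption | Door-to-door only | Figure 1 |
| Repeat within a week | None | Intervention; Figure 1 |
| Reading used as baseline | Not identified | nowhere |
| Months 1, 3, 6, 9, 12 | Home | Intervention; Follow-up |

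A non-home baseline is therefore permitted but not certain. A home month-12 reading is fixed.

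**Step 2. Size of the shift.** Let *s* be the share of participants whose baseline is taken outside the home, and *D* the mean systolic difference, non-home minus home. Then

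expected observed fall = true fall + *s* × *D*.

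The documents give neither *s* nor *D*. Both are assumed, including that *D* is positive. The comparison figure is the anticipated 7 mmHg fall (Sample size; Expected results).

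| *s* (assumed) | *D* (assumed), mmHg | Spurious fall, mmHg | Share of 7 mmHg |
|---|---|---|---|
| 0.25 | 3 | 0.25 × 3 = 0.75 | 11% |
| 0.50 | 5 | 0.50 × 5 = 2.5 | 36% |
| 0.75 | 8 | 0.75 × 8 = 6.0 | 86% |

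If *D* were negative, the same amounts would be subtracted and would hide a real fall.

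**Step 3. How small a shift would look significant?** Inputs from Sample size: SD 50, correlation 0.3, 1,912 participants before allowance for loss, two-sided 5%.

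- SD of the change = 50 × √(2 × (1 − 0.3)) = 59.16 mmHg.
- Standard error of the mean change = 59.16 / √1,912 = 1.35 mmHg.
- Shift that alone reaches significance = 1.96 × 1.353 = 2.65 mmHg.

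For the middle case of 2.5 mmHg and no true effect, the chance of a significant result is about Φ(2.5/1.353 − 1.96) = 0.455, against a nominal 0.05. With an assumed SD of 20 in place of 50, the standard error is 20 × √1.4 / √1,912 = 0.54 mmHg and that chance is 0.996.

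The figure 1,912 is used only as the plan's stated number. The paired formula with the plan's inputs gives (59.16 × 3.2415 / 7)² ≈ 751, so 1,912 is not reproduced for this design. That is a separate matter, and the present point does not depend on it.

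**The case against.** **The article is condensed.** The place of the repeat reading and the definition of baseline may stand in the full protocol, or in the screening flowchart, which is not shown. The baseline could be the repeat reading, or one taken later with the other baseline clinical data, and it could be at home. This stands as a limit: the point has to be conditional. It does not remove the point, because what the article does fix (several permitted entry settings, one follow-up setting, a within-person contrast and a model without setting) is enough to allow the bias.

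**Much of the text points to the home.** The Figure 1 caption says door-to-door, Table 1 names door-to-door visits and outreach but not facilities, and Table 2 has CHWs measuring pressure on home visits. The non-home share could be small. It is unknown, and the statements disagree.

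**The technique is well standardised.** A quiet room, five minutes' rest, validated automated devices and averaging the second and third of three readings apply to every reading, and CHWs take both the screening and the follow-up readings. This is not a physician's office compared with self-measurement. These steps should shrink a setting effect, but they do not equalise setting.

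**The limitations already cover attribution.** The Discussion concedes the missing comparator and the convenience sampling, but not a change of measurement setting, which, unlike those two, can be prevented.

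**Stronger readings the documents do not support:**

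- *That the entry readings precede consent.* The Intervention text says otherwise for the first: "After consent, individuals will undergo initial blood pressure measurement". A further informed consent then covers participation.
- *That follow-up pressure is read after counselling and so is lowered by it.* The Figure 3 caption does list counselling first ("At each visit, participants will receive health counseling, blood pressure measurement, weight monitoring, and a review of their pharmacological treatment"), but Table 1 names measurement before counselling for the same visits. Neither list sets a sequence.
- *That the bias certainly favours the intervention.* Event and clinic readings may run higher than home readings, but nothing in the article shows it.

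**Conclusion.** The point holds in conditional form. For participants whose baseline is taken outside the home, a setting difference may be counted as intervention effect on the primary outcome, and the plan as described neither prevents it, records it nor adjusts for it.

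Size and direction are unknown. Under the assumed ranges (25% to 75% with a non-home baseline, readings there 3 to 8 mmHg higher) the spurious fall is 0.75 to 6 mmHg, or 11% to 86% of the anticipated 7 mmHg. With the plan's own SD, correlation and sample size, a shift of about 2.65 mmHg would be significant without any true effect. If the baseline proves to be a home reading for everyone, the problem disappears.

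The plan should be changed on this point. The primary estimate is exposed, and a place that is never recorded cannot be reconstructed.

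**What to change.** 1. State that the repeat reading within a week, taken with the full Blood pressure measurement protocol, is the baseline for all blood pressure outcomes, and take it at the participant's home where feasible.
2. Add a REDCap field for the place of every reading, at entry and at follow-up.
3. Add a sensitivity analysis of the primary outcome restricted to participants with a home-measured baseline, and report the change separately for those with a non-home baseline. The two groups will also differ by recruitment channel, so the contrast between them is descriptive.
4. Reconcile the Intervention text, the Figure 1 caption and the Discussion on where screening occurs.

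**Cost.** Items 2 to 4 need wording, one database field and one extra model fit. Item 1 adds CHW travel at entry, because scheduled home visits start only after enrolment in a cardiovascular risk programme. A compulsory home repeat for everyone with a raised first reading would cost considerably more, since it would include people who are then not confirmed, on top of an enrolment target of 2,294. Hence *where feasible*, with the sensitivity analysis covering the rest. The estimated reduction may turn out smaller.

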**Figure 1 F1:**
[figure not shown]
RE-HOPE study flowchart. Trained CHWs, supported by recognized community leaders, will conduct a door-to-door active community-based case finding using a standardized screening protocol. If hypertension is detected, a follow-up measurement will be scheduled within a week. Participants with hypertension will be referred to their assigned primary care provider based on their health insurance affiliation, using a standardized referral form. Once enrolled in a cardiovascular risk management program, home visits will be scheduled as part of the community-based intervention. BP, blood pressure; CHW, community health workers; CV, cardiovascular.

Referral to primary care providers: Participants with hypertension will be referred to their assigned primary care provider based on their health insurance affiliation, using a standardized referral form. A centralized team will submit participant lists via an online platform (e.g., OneDrive) to schedule medical appointments and ensure program enrollment. Participants and/or their families will be contacted by phone with appointment details. If a participant does not attend, they will be followed up to identify barriers and facilitate access to care. If a participant does not agree to assist, they will be excluded. Once enrolled in a cardiovascular risk management program, home visits will be scheduled as part of the community-based intervention (Figure 2).

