
The “Implementation, Integration, and Institutionalization of a Community-Based Care Program to Reduce Cardiovascular Risk in Santander” (RE-HOPE) study will be developed to optimize community-level hypertension management by integrating CHWs into the processes of early detection, follow-up, and blood pressure control. The RE-HOPE model combines detection and referral mechanisms, structured health counseling, ongoing monitoring, and the use of simplified clinical algorithms to facilitate therapeutic decision-making and improve clinical outcomes.

Currently, cardiovascular risk programs at both the regional and national levels have gaps that limit their coverage. First, a high proportion of individuals with hypertension are unaware of their condition and therefore do not access cardiovascular risk programs; on the other hand, although some individuals with hypertension are aware of their disease, participation in institutional activities remains suboptimal. It is estimated that compliance with institutional programs is only around 60% (11). Additionally, among those already enrolled in cardiovascular risk programs, it is necessary to overcome some of the barriers identified by users in order to achieve hypertension control, including access to health services, coverage, education about the disease, and interaction with patients (12). The RE-HOPE model is designed to address these gaps by helping institutional cardiovascular risk programs increase their coverage. This will be achieved by strengthening patient engagement, reinforcing home-based health education, and improving continuity of care through more patient-centered strategies.

The distinguishing feature of the RE-HOPE study is the timely institutionalization of patients into cardiovascular risk management programs through structured coordination between community case detection and primary healthcare providers. We aim to develop an innovative and potentially scalable strategy that, if proven effective, may help close existing gaps in hypertension control in LMICs such as Colombia.

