	Inner context	Assessment of institutional readiness and implementation capacity in primary care centers	Research team, clinic managers	Feasibility	Number of primary care centers meeting readiness criteria	Readiness assessment checklist; pre-implementation
Preparation	Inner context	Training program for CHWs and nursing assistants on standardized BP measurement, counseling, referral procedures, and data entry	Research team, clinical trainers	Feasibility	Percentage of CHWs and nursing assistants completing certification training	Training attendance records; pre-implementation
	Inner context	Definition of operational workload for CHWs, including assignment of households and follow-up responsibilities	Research team, clinic managers	Feasibility	Mean number of households and participants assigned per CHW	Project operational records; pre-implementation
	Bridging factor	Coordination meetings between community teams and primary care cardiovascular risk programs	Research team, clinic managers	Adoption readiness	Number of coordination meetings conducted	Meeting minutes; pre-implementation
	Innovation factor	Development of standardized counseling materials and operational tools for home visits	Research team	Fidelity preparedness	Availability of standardized materials across participating clinics	Project documentation; pre-implementation
Implementation	Innovation factor	Community-based hypertension screening through door-to-door visits and outreach activities	CHWs, community leaders	Adoption	Number of individuals screened for hypertension per CHW	REDCap study database; implementation period
	Bridging factor	Referral pathway connecting community screening with cardiovascular risk programs in primary care	CHWs, primary care providers	Reach	Percentage of screened hypertensive individuals attending primary care appointment	Referral tracking system; implementation period
	Inner context	Delivery of structured home-based counseling sessions on hypertension management and lifestyle modification	CHWs	Fidelity	Proportion of planned home visits completed according to protocol	Visit checklists and REDCap records; implementation period
	Inner context	Monitoring and supervision of CHWs by nursing supervisors through periodic meetings and field visits	Nursing supervisors	Fidelity	Number of supervision meetings or field visits conducted per CHW	Supervision logs; implementation period

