### Outcomes and measurements

The primary outcome is the change in systolic blood pressure levels from baseline to 12 months.

Secondary outcomes include:
−Systolic and diastolic blood pressure levels from baseline to 12 months.−Proportion of participants achieving systolic blood pressure control (<140 mmHg) from baseline to 12 months.−Changes in the prevalence of healthy behaviors (including reduced tobacco use and alcohol consumption, and regular physical activity).−Proportion of non-institutionalized individuals with hypertension (i.e., those not enrolled in cardiovascular risk management programs).−Change in cardiovascular risk score using the WHO risk prediction tools (16).−Identification of barriers and facilitators related to cardiovascular risk management.−Change in CHWs' cognitive and attitudinal competencies, assessed through knowledge, attitudes, and practices questionnaires administered to primary care health personnel.

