#### Clinical effectiveness outcomes

Descriptive analyses will summarize continuous variables using means or medians, along with standard deviations or interquartile ranges, depending on the distribution of the data. Absolute and relative frequencies represent categorical variables. For the primary and secondary outcomes, the analysis will produce estimates using linear mixed models of the continuous outcomes (change in systolic blood pressure, systolic and diastolic blood pressure), and generalized linear mixed models for the categorical outcomes (proportion of hypertension control, proportion of modification of life styles, proportion of participants in low, moderate, high and extremely high cardiovascular risk), estimating mean and 95% confidence intervals at baseline and 3, 6, 9, and 12 months of follow-up. The models will include random intercepts accounting for within-subject correlation over time, and the fixed effects will include sex, region, age and anthropometric measures. We will impute missing covariate data using the predictive mean matching algorithm implemented in the mice package (version 3.16) in R statistical software (version 4.3). We will not impute missing outcome because these are expected to be approximately missing at random, primarily due to participants moving out of their municipality of residence. Accordingly, the mixed-effects model will be fitted using the observed data. Finally, we will perform a sensitivity analysis comparing the primary and secondary outcomes between participants who are aware of their condition and receiving treatment and those who are unaware of their condition. The mixed-effects models will be fitted using the lme4 (version 1.1-35.1) and mgcv (version 1.9-1) packages in R.

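### The 12-month blood pressure results cover only participants who were linked to primary care, because refusers are excluded after consent and follow-up visits begin only at programme enrolment

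*Protocol article*

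**What the plan says.** The order of steps is set out in the protocol article under Intervention.

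- **Consent and baseline.** In the component on identifying individuals: "Those meeting hypertension criteria will be invited to participate, and informed consent will be obtained". The next sentence adds: "Baseline sociodemographic and clinical data will also be collected".
- **Referral.** Participants are then referred to their assigned provider. A person who misses the appointment is contacted so that barriers can be found and access eased. The next sentence reads: "If a participant does not agree to assist, they will be excluded".
- **Start of follow-up.** "Once enrolled in a cardiovascular risk management program, home visits will be scheduled as part of the community-based intervention". The Figure 1 legend repeats this condition.
- **Outcome measurement.** The Follow-up section and the Figure 3 legend describe follow-up blood pressure only at the home visits (months 1, 3, 6, 9 and 12).

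The Introduction calls timely entry into cardiovascular risk programmes the study's distinguishing feature, and the Figure 2 legend lists referral as one of four components of the strategy. Outcomes and measurements includes a secondary outcome, "Proportion of non-institutionalized individuals with hypertension", explained there as people not enrolled in such programmes. Clinical effectiveness outcomes leaves missing outcomes unimputed, on the ground that they are roughly missing at random, "primarily due to participants moving out of their municipality of residence".

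**The concern.** Someone can be found by screening, meet the criteria, consent, give baseline data, and then be removed for declining primary care. With no home visits, that person has no follow-up reading. Membership of the group that yields the primary outcome thus depends on an event after baseline that the strategy is meant to bring about.

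The design is single-arm with within-participant comparisons, so no control group is subject to the same selection. If people who refuse care improve less than those who accept it, the reported fall in systolic pressure and the control rate will look better than the result of applying the strategy to everyone it finds and consents. The people at risk of removal are also close to the intended target: eligibility criterion (c) recruits known hypertensive individuals who do not attend programmes regularly, and the limitations paragraph of the Discussion says the strategy aims at people who do not usually use health services. That paragraph names the single arm, convenience sampling and the clinical exclusions, but not this selection.

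Two further results are touched. The non-institutionalized proportion is pushed downward if it is computed among those retained. The missing-at-random rationale, which rests on people moving away, does not cover people removed for refusing care.

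**Working it through.** **Step 1: the sequence.** As described, it runs: screening → consent and baseline data → referral → contact with non-attenders → exclusion of those who still do not agree → programme enrolment → home visits with blood pressure. The exclusion comes after consent and before any follow-up reading. If 'assist' means something other than attend, it is still a post-consent exclusion at the referral step.

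**Step 2: what a later analysis could repair.** Under the stated rule an excluded person has at most a baseline value. A mixed model fitted to observed data can use that value, but it has no outcome data from refusers with which to estimate their change. An analysis plan written later cannot supply readings that were never taken.

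**Step 3: size for systolic pressure.** The article gives no refusal rate and no expected change in refusers, so this is an illustration.

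Inputs:
- 7 mmHg fall in enrolees: the reduction assumed in Sample size and Expected results.
- p, the share of consented participants who are linked: assumed 0.6 to 0.9.
- e, the fall in those excluded: assumed 0 to 4 mmHg.

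Formula: fall over all consented = p × 7 + (1 − p) × e.

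| p | e = 0 | e = 4 |
|---|---|---|
| 0.9 | 0.9 × 7 = 6.3 | 6.3 + 0.1 × 4 = 6.7 |
| 0.8 | 0.8 × 7 = 5.6 | 5.6 + 0.2 × 4 = 6.4 |
| 0.6 | 0.6 × 7 = 4.2 | 4.2 + 0.4 × 4 = 5.8 |

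The range is 4.2 to 6.7 mmHg. If e = 7, the result is 7 for every p and there is no bias.

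**Step 4: size for control.** Take the article's 60% target as the rate in enrolees, and assume that 0–30% of those excluded are controlled.

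- p = 0.8: 0.8 × 60 = 48%, up to 48 + 0.2 × 30 = 54%.
- p = 0.6: 0.6 × 60 = 36%, up to 36 + 0.4 × 30 = 48%.

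**Step 5: is power at stake?** On the stated inputs (SD 50, correlation 0.3, 7 mmHg, 90% power, two-sided 5%), the paired formula gives n = [50 × √(2 × 0.7) × (1.960 + 1.282) / 7]² ≈ 751. This does not reproduce the article's 1,912, which is a separate matter. If 40% were excluded from within the 2,294 and 20% of the rest lost, 2,294 × 0.6 × 0.8 ≈ 1,101 would remain, still above 751. The issue is selection, not precision.

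**The case against.** The strongest reply has several parts.

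- **Selection is on linkage, not on response.** A reader might infer that effectiveness is estimated only in people for whom the strategy worked. The article does not support that: enrolees whose pressure does not fall remain in the analysis.
- **Non-attendance alone does not exclude.** The person is first contacted and helped; only continued refusal leads to removal. This stands and probably reduces the number excluded.
- **Linkage failure is reported elsewhere.** A reader might infer that the Reach indicator is distorted. Table 1 defines it as "Percentage of screened hypertensive individuals attending primary care appointment", so its denominator is people screened and a later refuser still counts as a non-attender. That indicator is sound as defined, but it does not put refusers back into the blood pressure estimate.
- **The missing-data rationale is not contradicted.** It says mainly, not only, and concerns missing outcomes in people who are analysed. It is silent on these exclusions, which is a gap.
- **The non-institutionalized proportion need not approach zero.** The article gives no denominator, and enrolees may leave programmes during the year. The downward push is conditional.
- **The size is assumed.** The Introduction's estimate that "compliance with institutional programs is only around 60"% describes existing programmes, the gap the study wants to close. It is not a refusal rate among people who have consented and been helped to attend. Zero change in refusers is also an extreme: most were recruited on a raised reading, so some fall by regression to the mean is likely.
- **Analysis sets are often left to the analysis plan.** That is true of naming the set. It does not answer a stated rule under which the readings are never obtained.

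**Conclusion.** The point holds as one about whom the result describes. As written, the 12-month systolic change and control rate apply to consented participants who were successfully linked to primary care, not to all those the strategy identified and consented, although linkage is part of the strategy under test. This follows from the stated rules and does not depend on any figure.

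The size cannot be fixed from the article. The ranges of 4.2–6.7 mmHg against 7 mmHg, and 36–54% control against 60% (at 60–80% linkage), rest wholly on the assumed linkage shares and outcomes in those excluded. The bias would be nil if excluded and enrolled participants changed equally. A claim that the study would be underpowered, that Reach is distorted or that the missing-data rationale is contradicted would go beyond the text.

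**What to change.** 1. Remove the post-consent exclusion from the analysis, and define the primary analysis set as all consented hypertensive participants with a baseline blood pressure.
2. Offer at least the month-12 measurement to everyone in that set regardless of programme enrolment, timed from baseline, since people who are never linked have no enrolment date. Redefining the set without collecting these readings would not be enough.
3. Treat those who also decline measurement as missing, not excluded. Add a sensitivity analysis for departures from missing at random among non-linked participants, over a range of assumed changes. Assigning zero change to everyone without a month-12 reading would be arbitrary, because it would also apply to people who moved away.
4. Count refusers as non-institutionalized in the secondary outcome and state its denominator.
5. Report the enrolled-only estimate as a secondary result, labelled as such.

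The cost is a change of wording, some additional measurement visits by community health workers to people who have already consented, and possibly a less favourable estimate. The month-12 reading has to be arranged prospectively, because it cannot be recovered afterwards.
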